## Methods

### Study design

This cRCT evaluates the effectiveness of 4 different combinations of the selected pre- and post-natal nutrition-specific interventions for improving children’s linear growth, compared to the comparison arm with usual practices. The three types of BCC are combined into one ‘BCC’ intervention and delivered universally in all four intervention arms. Profile of the four intervention arms are – intervention arm 1: BCC with PNS and CFS; intervention arm 2: BCC with PNS; intervention arm 3: BCC with CFS; intervention arm 4: BCC alone. (Fig. 1
**)**. The cohort of the mother-child dyads will be followed-up over the intervention period of ~36 months starting from recruitment to 24 months of child’s age.

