#### Nutritional supplements for pregnant women

A lipid-based nutritional supplement (LNS) developed by Nutriset™, packed in ~20 g sachets, is provided to pregnant women. The formulation contains vegetable fat (soy), skimmed milk powder, peanuts, vitamin and mineral complex, sugar, stabilizer: fully hydrogenated vegetable fat, and antioxidant: tocopherols. An additional file details the components (see Additional file 1). Each sachet contains 70–75% of the recommended dietary allowance (RDA) for most of the micronutrients, and partial provision of protein and lipids, including essential fatty acids. The dose is one sachet per pregnant woman per day throughout pregnancy.

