#### Complementary food supplements for children

Another LNS formulation developed by Nutriset™, packed in each ~10 g sachets, is provided to be fed to children from 6 to 23 completed months of age. The formulation contains vegetable fat, skimmed milk powder, peanuts, sugar, vitamin and mineral complex, maltodextrin, and emulsifier: lecithin. An additional file details the components (see Additional file 2). Each 20 g of LNS contains 70–75% of RDA for most of the micronutrients, and partial provision of protein and lipids, including essential fatty acids. The dose is two sachets per child per day, starting from 6 completed months of age (180 days) continued till 23 completed months.

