### Trial outcomes and measurements

#### Primary outcomes

The primary outcome measure will be the LAZ of children at 24 months of age based on WHO MGRS 2006 child growth reference. This will be calculated from the child’s age in months and length on associated ages. Length is measured at age 7–10 days, then monthly from 1 to 6 months, and at 9^th^, 12^th^, 15^th^, 18^th^, 21^st^ and 24^th^ months of age, with locally manufactured collapsible length boards (precision 1 mm).

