### Statistical analysis plan

Data analysis to detect change of the primary outcome (mean LAZ) will be conducted with length measured at 1, 3, 6, 9, 12, 15, 18, 21 and 24 months of age using t-tests assuming LAZ will satisfy the normality assumption. Longitudinal assessment of significance using lag time of stunting (mean length > −2SD below median of WHO reference population) will be done by the log rank test, followed by fitting a Cox proportional hazards model for each intervention arm to determine the change in risk of stunting compared to the comparison arm. Multiple linear regression will be employed to quantify the effect of intervention in each intervention arm compared to the comparison arm in terms of mean LAZ change and some secondary continuous outcome measures including changes in mother’s weight, birth weight, diarrhoea morbidity. Logistic regression will be used on binary outcome variables which comprise most of our secondary outcomes measures (e.g. – EBF and breastfeeding initiation within 1 h of birth). All these models will be controlled for possible confounders (household food security, educational background and SES) if randomisation of the clusters does not control for differences in these factors at baseline. For regression models, we shall consider random effects of clustering. All analysis will be intention-to-treat. Quantitative data analysis will be done using Stata SE 14.2 (StataCorp LP, College Station, Texas, USA).

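### Before complementary food supplementation starts, arms 1 and 2 have the same planned treatment, as do arms 3 and 4; analysing early outcomes arm by arm is valid but gives up precision that pooling would recover

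*Protocol article*

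**What the plan says.** Study design defines the arms as "intervention arm 1: BCC with PNS and CFS; intervention arm 2: BCC with PNS; intervention arm 3: BCC with CFS; intervention arm 4: BCC alone", and says the BCC component is "delivered universally in all four intervention arms".

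The supplements are given at different times. For PNS, "The dose is one sachet per pregnant woman per day throughout pregnancy". CFS is given to the child "starting from 6 completed months of age (180 days) continued till 23 completed months".

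Statistical analysis plan: "Multiple linear regression will be employed to quantify the effect of intervention in each intervention arm compared to the comparison arm". This covers mean LAZ change and "some secondary continuous outcome measures including changes in mother’s weight, birth weight, diarrhoea morbidity". The same section lists t-tests of LAZ at ages that include 1, 3 and 6 months. Binary secondary outcomes, "e.g. – EBF and breastfeeding initiation within 1 h of birth", go to logistic regression.

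Sample size explains that the comparison arm was doubled to give more power for secondary outcomes, and describes those outcomes as examined between the comparison arm and an individual intervention arm. The article nowhere combines arms 1 and 2, or arms 3 and 4, for any outcome.

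**The concern.** Up to the start of CFS the five arms contain only three planned treatments: BCC+PNS, BCC, and routine services. Gestational weight gain, birth weight, early initiation of breastfeeding, exclusive breastfeeding and early LAZ are all determined, or largely determined, in that period. The stated contrast estimates each of two early effects twice, each time from 25 of the 50 clusters that carry the information. The estimates are less precise than they could be, there are more tests than distinct questions, and two arms with the same treatment may land on different sides of the significance threshold. This matters because the Discussion says the trial will explore gestational weight gain, birth weight and feeding practices, and will inform whether prenatal supplementation should be prioritised.

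**Working it through.** **Treatment content by period**

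| Arm | Pregnancy | Birth to 180 days | From 180 days |
|---|---|---|---|
| 1 | BCC+PNS | BCC | BCC+CFS |
| 2 | BCC+PNS | BCC | BCC |
| 3 | BCC | BCC | BCC+CFS |
| 4 | BCC | BCC | BCC |
| 5 | routine | routine | routine |

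Arms 1 and 2, and arms 3 and 4, have the same planned history until the third period. Diarrhoea morbidity, named in the regression sentence, is recorded on both sides of CFS start and is not counted here.

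**Inputs**

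- From Sample size: ICC 0.06, SD 1, 5% alpha, 11% pregnancy loss, 25 clusters per arm.
- From Participant recruitment: 10 women per intervention cluster, 20 per comparison cluster.
- Assumed: two-sided test; ICC 0.06 carried over from height-for-age to the early outcomes; continuous outcomes in SD units; pregnancy loss the only loss before birth; normal approximation; union blocks ignored.

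**The plan's own sample size.** The enrolment step reproduces: losses of 11% + 4% + 15% = 30%, and 175/0.70 = 250. The 175 does not follow from the stated inputs. At 80% power, 99 per arm × (1 + 6 × 0.06) gives about 135. The stated figure is larger than needed, so this does not weaken the trial and has no bearing on the present point.

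**Standard errors at birth**

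- Births per cluster: 10 × 0.89 = 8.9 (intervention) and 20 × 0.89 = 17.8 (comparison). Births per arm: 222.5 and 445.
- Variance of one intervention arm mean: (1 + 7.9 × 0.06)/222.5 = 1.474/222.5 = 0.00662.
- Variance of the comparison arm mean: (1 + 16.8 × 0.06)/445 = 2.008/445 = 0.00451.
- One arm versus comparison: √(0.00662 + 0.00451) = 0.106.
- Pooled pair versus comparison: √(0.00331 + 0.00451) = 0.088.
- Variance ratio: 0.00782/0.01114 = 0.70, so about 30% lower.
- Arms 1+2 versus 3+4: √(2 × 0.00331) = 0.081. A single arm against a single arm gives √(2 × 0.00662) = 0.115.

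**Detectable difference at 80% power**, (1.96 + 0.84) × SE: 0.30 SD for one arm and 0.25 SD pooled.

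**Discordance between two identically treated arms.** The two estimates share the comparison arm, so their correlation is 0.00451/0.01114 = 0.405. From the bivariate normal, P(exactly one significant) = 2 × [P(one given arm significant) − P(both significant)].

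| True effect (assumed) | Power, one arm | Power, pooled | Both significant | Exactly one significant |
|---|---|---|---|---|
| 0.20 SD | 47% | 62% | 29% | 37% |
| 0.25 SD | 66% | 81% | 49% | 33% |
| 0.30 SD | 81% | 92% | 69% | 24% |
| 0.40 SD | 97% | 99.5% | 94% | 6% |

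**Sensitivity.** At the effect for which one arm has 80% power, discordance stays at 24–26% for ICC from 0.001 to 0.10. At a fixed 0.25 SD it is 20% at ICC 0.001, 27% at 0.02 and 36% at 0.10.

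**The case against.** The strongest reply is that comparing each randomised arm with the comparison arm is valid and unbiased, so this is an efficiency preference. That stands. The plan also took a step for secondary outcomes by doubling the comparison arm, and one arm can already detect about 0.30 SD at birth. The discordance figures depend on effect sizes the documents do not give for these outcomes. At 0.4, the only planned effect (stated for LAZ at 24 months), discordance is about 6%. No figure is computed for the binary breastfeeding outcomes. An analysis plan that is not shown may group the arms; still, the contrast stated in the article is arm by arm.

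Several stronger readings are tempting, and the documents do not support them:

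- A reader might infer that half the information is thrown away. All arms are analysed; the cost is the 30% in variance.
- A reader might infer opposite verdicts on the same bundle. The discordance is significant versus not significant. Significant effects in opposite directions have probability below 0.01% under the null.
- A reader might infer that every early outcome is fixed arm by arm. The regression sentence does this for LAZ and some continuous outcomes. The t-test and logistic sentences name no contrast, and the general wording in Sample size serves to justify the doubled arm.
- A reader might infer that the plan would report a chance split as a difference between bundles. It sets no arm 1 versus arm 2 test and no such reading rule.
- A reader might call it an error that length is measured at 7–10 days ("Length is measured at age 7–10 days, then monthly from 1 to 6 months") but LAZ is analysed only from 1 month. The analysis list also skips 2, 4 and 5 months. It selects among measured ages and contradicts nothing.

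**Conclusion.** The point holds as a worthwhile, cheap improvement, not as an error that invalidates an analysis. For outcomes measured before CFS starts, the stated contrast separates arms whose planned treatment is the same. The cost is a standard error of 0.106 instead of 0.088, a detectable difference of 0.30 SD instead of 0.25 SD, and, for true effects of 0.20 to 0.30 SD, a 24–37% chance that two identically treated arms differ in significance. The standard errors and detectable differences rest on ICC 0.06 applying to the early outcomes, SD units and 11% pregnancy loss; the discordance figures also need an assumed effect size. The comparison at 24 months is untouched, because by then all four bundles differ.

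**What to change.** Add to Statistical analysis plan that, for gestational weight gain, birth weight, early initiation of breastfeeding, exclusive breastfeeding and LAZ measured before CFS starts, the main contrasts are arms 1+2 (50 clusters) versus comparison (25 clusters) and arms 3+4 (50 clusters) versus comparison, with arms 1+2 versus 3+4 for the effect of PNS. Include 6-month LAZ only where the measurement falls before or at CFS start, since the visit could otherwise follow the first supplement. Keep the arm-by-arm contrast for outcomes after CFS starts, and tabulate single-arm early results descriptively. Clusters were randomised in blocks of five with one per arm, so each block contributes 2:2:1 clusters to the three groups and the pooled contrasts keep the randomisation.

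The cost is wording, with no new data. Recruitment closed in May 2016, so many early outcomes will already have been collected. The change should therefore be a dated amendment that says whether any early results by arm had been seen. The one downside is that allocation was not concealed, so expecting CFS later could slightly alter early behaviour in arms 1 and 3; the descriptive single-arm table would help to show this.

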**Methods:**

This community-based cluster randomised trial (c-RCT) compares 4 intervention combinations against one comparison arm. Intervention combinations are: 1) Behaviour change communication (BCC) on maternal nutrition during pregnancy, exclusive breastfeeding, and complementary feeding, along with prenatal nutritional supplement (PNS) and complementary food supplement (CFS); 2) BCC with PNS; 3) BCC with CFS; and 4) BCC alone. The comparison arm receives only routine health and nutrition services. From a rural district, 125 clusters were selected and randomly assigned to any one of the five study arms by block randomisation. A bespoke automated tab-based system was developed linking data collection, intervention delivery and project supervision. Total sample size is 1500 pregnant women, with minimum 1050 resultant children expected to be retained, powered to detect a difference of at least 0.4 in the mean LAZ score of children at 24 months, the main outcome variable, between the comparison arm and each intervention arm. Length and other anthropometric measurements, nutritional intake and other relevant data on mother and children are being collected during enrolment, twice during pregnancy, postpartum monthly till 6 months, and every third month thereafter till 24 months.

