### Relevance of the present study

We have adapted five *preventive* interventions to create our own interventions bundles, based on Bhutta et al.’s list considering feasibility of scale-up in low resource settings and targeting the first 1000 days of life (from conception to two years of age). Our interventions include, a) Behaviour change communication (BCC) on nutrition and health-related practices during pregnancy; b) BCC on exclusive breastfeeding (EBF) for postnatal first 6 months; c) BCC on age-specific complementary feeding (CF) with continued breastfeeding thereafter till 23 completed months; d) Nutritional supplementation during pregnancy (PNS) with preventive doses of micronutrients, and partial provision of protein and lipids; e) Nutritional supplementation for children (CFS) during 6 to 23 completed months of age, with preventive doses of micronutrients, and partial provision of protein and lipids. In essence, this randomized controlled trial provides a crucible to see how different nutritional interventions interact when delivered in bundled packages in community settings to affect linear growth of the child from conception to two years of age compared to the comparison arm where routines practices will run unhindered.

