### Study aim and hypothesis

This study aims to test the effectiveness of the intervention bundle(s) on improving length-for-age Z score (LAZ) of children at two years of age. We hypothesised that our intervention bundle(s) would cause a change of at least 0.4 in mean LAZ of children, translating to at least 30% reduction in stunting in that arm(s), compared to that in the comparison arm.

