Recently, the government of Bangladesh undertook significant efforts to digitize service delivery in all spheres of health systems including frontline and community level health care providers who are responsible for delivering nutrition interventions [39]. This trial will provide a timely and pertinent contribution to the knowledge base of use of electronic platforms in not only recording and reporting of service utilization but also aiding the community workers in nutrition service delivery at scale.

A limitation of our study includes not being able collect biological samples from study participants due to funding constraints; this would have allowed us to investigate potential biological mediators of the effect of nutrients as well as exploring inherited differences in metabolism predisposing to the risk of stunting. Our study also does not look at knock-on effects beyond 2 years of age.

We anticipate that the results from this cRCT will have policy-level implications in prioritizing a set of interventions when addressing stunting - whether it is behaviour change communication only or combined with prenatal and/or post-natal nutritional supplementation.

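### Every contrast the plan names is against the comparison arm, but the article anticipates conclusions about differences and interaction between the bundles

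*Protocol article*

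**What the plan says.** Study design sets out arm 1 as BCC with both supplements, then "intervention arm 2: BCC with PNS; intervention arm 3: BCC with CFS; intervention arm 4: BCC alone". BCC is given in all four, so arms 1 to 4 are PNS yes/no crossed with CFS yes/no on a BCC background. Arm 5 receives routine services.

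The formal hypothesis concerns each bundle against the comparison arm: "We hypothesised that our intervention bundle(s) would cause a change of at least 0.4 in mean LAZ of children". The abstract states power for a difference "between the comparison arm and each intervention arm", and the Sample size section doubles arm 5 to strengthen that comparison for secondary outcomes.

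In the Statistical analysis plan, two sentences name the arms compared. Linear regression is used "to quantify the effect of intervention in each intervention arm compared to the comparison arm in terms of mean LAZ change", and a Cox model is fitted "for each intervention arm to determine the change in risk of stunting compared to the comparison arm". No contrast among arms 1 to 4, no PNS or CFS main effect and no PNS by CFS term is named.

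Two other statements go further. Relevance of the present study says the trial "provides a crucible to see how different nutritional interventions interact when delivered in bundled packages in community settings". The Discussion expects the results to inform which interventions to prioritise, "whether it is behaviour change communication only or combined with prenatal and/or post-natal nutritional supplementation".

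**The concern.** Whether a supplement adds to BCC is a question about arms 1, 2 and 3 against arm 4. Whether the supplements interact is a question about all four together. Four separate tests against arm 5 address neither. If arm 1 differs significantly from arm 5 and arm 4 does not, that is no evidence that arm 1 differs from arm 4, because the difference between them has not been tested.

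At stake is the policy message. If the only formal results are four comparisons with arm 5, a reader choosing between counselling alone and counselling with supplements has little else to go on than which of the four were significant.

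**Working it through.** **Inputs** (Sample size section): SD 1; intra-cluster correlation 0.06; 25 clusters per arm; 175 children in each intervention arm (7 per cluster) and 350 in the comparison arm (14 per cluster); 5% alpha, taken as two-sided because the article does not say; 80% power.

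**1. The plan's own figure.** Without clustering, n = 2(1.960 + 0.842)²/0.4² = 98.1 per arm. Times the design effect at 7 per cluster, 1 + 6 × 0.06 = 1.36, this is 133. Solving instead for 25 fixed clusters gives 98.1 × 0.94/(25 − 98.1 × 0.06) = 4.83 per cluster, about 121. The stated 175 is therefore not reproduced at 80% power. It is on the safe side, and this point does not depend on it. The total does reproduce: 4 × 175 + 350 = 1050. The steps below take 175 and 350 as given.

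**2. Variance of an arm mean.** Intervention arm: 1.36/175 = 0.00777. Comparison arm: (1 + 13 × 0.06)/350 = 1.78/350 = 0.00509.

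**3. Precision of each contrast.** Detectable difference at 80% power = 2.802 × SE (normal approximation).

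| Contrast | SE | Detectable | Power at 0.4 | Power at 0.2 |
|---|---|---|---|---|
| One arm v comparison (planned) | √(0.00777 + 0.00509) = 0.113 | 0.32 | 94% | 42% |
| Arm 1, 2 or 3 v arm 4 | √(2 × 0.00777) = 0.125 | 0.35 | 89% | 36% |
| PNS or CFS main effect (350 v 350) | √(2 × 1.36/350) = 0.088 | 0.25 | 99.5% | 62% |
| PNS by CFS interaction | √(4 × 0.00777) = 0.176 | 0.49 | 62% | 20% |

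A t approximation on cluster degrees of freedom lowers these powers by about 1 percentage point. Over an assumed intra-cluster correlation of 0 to 0.10, the detectable differences are 0.30 to 0.38 (arm v arm 4), 0.21 to 0.27 (main effect) and 0.42 to 0.54 (interaction).

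**4. How often equal bundles would look unequal.** Give all four bundles the same true effect. The four test statistics share the comparison arm, so any two correlate at 0.00509/(0.00777 + 0.00509) = 0.40. Drawing the five arm means from normal distributions with the variances in step 2 and counting trials where one, two or three of the four tests are significant gives:

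- true effect 0.40 (the plan's own): about 18%
- true effect 0.30 (assumed): about 52%
- true effect 0.25 (assumed): about 64%

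Repeating the draws at the plan's 0.4 with an assumed intra-cluster correlation of 0 or 0.10 gives about 3% and 29%.

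**The case against.** The strongest reply is that the plan does what its aim requires. The only section headed as aim and hypothesis concerns bundle against comparison arm, and the power statement, sample size and named regressions follow it. The sentence about interaction is background prose that itself ends by referring to the comparison arm, and the prioritisation sentence only anticipates policy use. Secondary contrasts are often left to a fuller analysis plan. This protects the primary analysis, which is not in question. It does not remove the mismatch: the article states what the trial will show, and no contrast it names would show it.

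Four stronger readings are tempting, and the documents support none of them.

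- *The trial cannot answer these questions.* It can. With arm indicators in the regression, differences between bundles are linear combinations of the coefficients. What is missing is their naming in advance.
- *Every planned test is against the comparison arm.* Only the Cox and linear regression sentences name that pairing. The t-test, log-rank and logistic sentences name no pair of arms.
- *The investigators will rank bundles by significance.* No passage says so. The abstract expects to learn which bundles have a significant effect, which is a statement about each bundle separately.
- *The factorial main effects are the most precise contrasts available.* All four BCC arms pooled against the comparison arm would have SE √(0.00777/4 + 0.00509) = 0.084, below 0.088.

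It is also fair to say that the larger discordance figures rest on effects the article does not use, so 18% is the one to lead with. Finally, the interaction's detectable difference of 0.49 exceeds the 0.4 the trial was designed for, so that question would be answered only imprecisely.

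**Conclusion.** The concern holds as a mismatch between the contrasts named and the conclusions anticipated. It is not a fault in the primary analysis or the design. With the plan's own inputs and a common true effect of 0.4, equal bundles would give a mixed pattern of significance in about 18% of trials, and in more if the effect is smaller. The planned sample gives 89% power to detect a 0.4 difference between a supplemented arm and BCC alone, and 80% power for a main effect of 0.25, but only about 62% for an interaction of 0.4.

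These figures assume SD 1, intra-cluster correlation 0.06, 7 and 14 children analysed per cluster, a two-sided 5% level with no multiplicity adjustment, and no gain from blocking by union or from covariates. That PNS or CFS adds to BCC is a fair reading of the Discussion, not a listed objective; interaction is stated outright.

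**What to change.** In the Statistical analysis plan, name these secondary contrasts for LAZ at 24 months, all from the cluster-adjusted regression:

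- arms 1, 2 and 3 each versus arm 4, which directly address BCC alone or with supplements;
- the PNS main effect (arms 1 and 2 v 3 and 4) and the CFS main effect (arms 1 and 3 v 2 and 4), noting that each averages over the other supplement;
- the PNS by CFS interaction, as an estimate with its confidence interval and described as imprecise.

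State that one bundle will be called better than another only on these contrasts. Either give a multiplicity approach for them or present them as estimates with intervals. The alternative is to narrow the statements on interaction and prioritisation to what comparisons with arm 5 can show.

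The cost is small: no new participants or data, only further contrasts from a model already planned. Follow-up was still under way when the article appeared, so they could be fixed before the 24-month results were known. The downside is several extra secondary contrasts to report and an interaction with SE 0.176 that may settle little.

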Several assumptions were considered for the sample size calculation [26]. The first assumption was that mean LAZ (our primary outcome variable) for 18–23 months old children in the comparison arm will be −2.0, and standard deviation of mean LAZ in both intervention and comparison arms will be 1, based on the mean HAZ reported in this age group in the BDHS 2011. These BDHS 2011 [25] parameters were the latest available during this protocol development. The estimates were still valid in 2015 since the latest BDHS (2014) showed similar stunting rates in *Sylhet* division [11]. Second, a 0.4 difference in mean LAZ score was expected in intervention arms compared to comparison. As the third assumption, we considered an 80% power and 5% alpha; the inter-cluster correlation coefficient of 0.06, derived from the design effect for HAZ in BDHS 2011, was used for adjustment of clustering effects. Fourth, the ratio between 4 intervention and 1 comparison arms was set at 1:1:1:1:1. Taking all the above assumptions into account, the Stata SE 13 software calculated the sample size to be 175 children per arm, which can be yielded from 25 clusters. However, to examine the secondary outcome variables between the comparison arm and individual intervention arm with a higher statistical power, the sample size in the comparison arm was doubled, thus the ratio between participant numbers in each intervention arm and comparison arm was raised to 1:2, respectively. The final allocation ratio of study participants was thus 1:1:1:1:2 for intervention arm 1: intervention arm 2: intervention arm 3: intervention arm 4: comparison arm 5. Thus, the final sample size was 175 children in each intervention arm and 350 children in the comparison arm. Considering the characteristics of the intervention, however, enrolment was during pregnancy. We therefore considered the following losses- 11% pregnancy loss due to abortion and still births (personal communication from Health and Demographic Surveillance System run by icddr,b at Mirzapur, Tangail), a 4% mortality in the first two years of life [25], 15% losses due to non-consent to participate by eligible women and loss-to-follow up. Loss-to-follow up includes refusal and migration out of study area. Thus, final sample size considering participant recruitment during pregnancy was 250 pregnant women in each intervention arm and 500 pregnant women in the comparison arm which is expected to yield the required number of children at 24 months from the enrolled cohort.

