#### Other measurements

Background characteristics of study participants: Information on demographic and socio-economic status (SES), family members, reproductive and morbidity history of pregnant women were collected using a structured questionnaire [25]. Household food security (HFS) information was collected through a questionnaire adapted from food security and nutrition surveillance tool [34]. These were recorded once during recruitment of the pregnant women after consent has been taken, to compare background characteristics between the arms.

Water sanitation and hygiene (WASH) and Knowledge attitude and practice (KAP): A questionnaire on the core indicators on water, sanitation and hygiene (WASH) was developed based on a standard manual for WASH [35]. Woman’s knowledge, attitude and practices (KAP) regarding maternal and child nutrition was developed based on WHO-recommended IYCF indicators and KAP manual [36]. WASH and KAP are collected during pregnancy and postpartum follow up visits.

Childhood morbidity: Morbidity, especially diarrhoea, directly impedes growth, while better hygiene practices lower infectious disease burden [37]. Therefore, children’s morbidity data is collected every month from postnatal 1 to 6 months and every three months thereafter till 24 months, using a 2-week recall questionnaire [11]. Vaccination data would be collected at 12 and 15 months based on EPI schedule.

Additional anthropometric measurements: Mother’s height is measured during recruitment for body mass index (BMI) calculation during early pregnancy. Mother’s mid-upper arm circumference (MUAC) (precision 1 mm), infant’s head circumference (during 1–6 moths age) and infant’s MUAC (during 7–24 months) are collected during follow-up visits, for associated z-score calculations.

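### Covariate adjustment of the regression models depends on observed baseline differences, with no criterion; one covariate set should be fixed in advance

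*Protocol article*

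**What the plan says.** The Statistical analysis plan section of the protocol article tests mean LAZ at nine ages by t-tests. It then says "Multiple linear regression will be employed to quantify the effect of intervention in each intervention arm compared to the comparison arm", for LAZ and some continuous secondary outcomes. Logistic regression serves the binary outcomes, and a Cox model for time to stunting is named earlier in the same paragraph.

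The covariate sentence follows: "All these models will be controlled for possible confounders (household food security, educational background and SES", with the bracket then closed and the condition added: "if randomisation of the clusters does not control for differences in these factors at baseline". No test, threshold or unit of decision (overall, per arm or per model) is given. Clustering is covered by "For regression models, we shall consider random effects of clustering".

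Under Other measurements, demographic, SES and food-security data are recorded at recruitment "to compare background characteristics between the arms". The same section says that the mother's "height is measured during recruitment for body mass index (BMI) calculation during early pregnancy". The article does not place height in any model.

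**The concern.** This is a rule that the document lays down, not a detail left open for a later plan, and it is a weak rule for three reasons.

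- **It uses the wrong criterion.** Adjustment helps when a covariate predicts the outcome. The size of its baseline difference between arms does not show that. A predictive covariate improves precision even when balanced, and that is the case in which the rule drops it.
- **It cannot be reproduced.** With no criterion, two analysts can both follow the sentence and report different regression estimates.
- **It need not give one model.** The trial is meant to show which bundles work. The text leaves open whether all four comparisons with the comparison arm carry the same covariates.

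In the logistic models, and the Cox model if the sentence covers it, adding a predictive covariate also changes the odds or hazard ratio being estimated. There the baseline table would partly decide the target as well as the precision.

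**Working it through.** **Inputs from the Sample size section.** "a 0.4 difference in mean LAZ score was expected in intervention arms compared to comparison"; "standard deviation of mean LAZ in both intervention and comparison arms will be 1"; intra-cluster correlation (ICC) 0.06; 80% power; 5% alpha (taken as two-sided); 25 clusters per arm; 175 children per intervention arm (175/25 = 7 per cluster) and 350 in the comparison arm (350/25 = 14 per cluster).

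**The plan's own figure.** Without clustering, n = 2 × ((1.960 + 0.842)/0.4)² = 98.1 per arm. With 7 per cluster the design effect is 1 + 6 × 0.06 = 1.36, giving 133.4, so 134 rather than the stated 175. A cluster size of 14 (design effect 1.78) gives 174.6. The loss allowance does reproduce: 250 × (1 − 0.30) = 175. The stated size errs on the large side, and nothing below depends on how it was reached.

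**How often chance alone would trigger adjustment.** Assumption: each of the three factors is tested at 5%, independently.

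- One contrast: 1 − 0.95³ = 0.143.
- Four contrasts, 12 tests: 1 − 0.95¹² = 0.460.

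The 12 tests are not independent, because the comparison arm is shared. For a factor with ICC 0.06, two contrasts correlate at (0.06 + 0.94/14)/(0.321, derived below) = 0.127/0.321 = 0.40. A normal simulation with that correlation gives about 42%. If the three factors also correlate at 0.3 to 0.5 (assumed), it gives about 41% to 38%. So 46% is a ceiling.

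**What the rule does to the LAZ estimate.** 4,000 simulated trials per effect size; one contrast of 25 v 25 clusters with 7 and 14 children; ICC 0.06, treated as known. Assumed R² is 0.04 for each listed factor and 0.09 for height, acting at both child and cluster level. Factors are screened at 5%.

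| Strategy | SD of estimate (true effect 0.3) | Power, 0.3 | Power, 0.4 | Type I error |
|---|---|---|---|---|
| Never adjust | 0.1135 | 74% | 94.7% | 4.1% |
| Conditional rule | 0.1115 | 75% | 94.8% | 3.8% |
| Always adjust for the three | 0.107 | 79% | 96.3% | 4.2% |
| The three plus height | 0.101 | 83% | 97.8% | 4.6% |

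Mean estimates for a true effect of 0.3 ran from 0.300 to 0.301 in all four rows, so there is no average bias. The conditional rule stays close to no adjustment.

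**What height alone could add.** The documents give no correlation r between maternal height and LAZ; 0.2 to 0.4 is assumed. Let height explain child-level variance only. The contrast variance is V/25, with

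V = 2 × 0.06 + 0.94 × (1 − r²) × (1/7 + 1/14).

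| r | V | Standard error | Reduction | Power for 0.4 |
|---|---|---|---|---|
| 0 | 0.321 | 0.1134 | – | 94.2% |
| 0.2 | 0.313 | 0.1120 | 1.3% | 94.7% |
| 0.3 | 0.303 | 0.1101 | 2.9% | 95.3% |
| 0.4 | 0.289 | 0.1076 | 5.1% | 96.1% |

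If height explained the cluster-level part in the same proportion, the reduction would be 1 − √(1 − r²), or 2% to 8%. The simulation makes that more favourable assumption.

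**The case against.** The best defence is that little harm follows. The t-tests that detect change in LAZ carry no covariates, so the rule cannot alter them. The rule does no worse than leaving covariates out, and power for the design difference is already high. The text names no significance test and gives a single list for all models, which can be read as one decision rather than twelve. Maternal height is a further precision covariate, and a condensed article may leave that choice to a fuller plan. All of this stands. It limits the size of the point but does not supply the missing criterion or make imbalance a sound reason to adjust.

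It could also be said that imbalance here may not be pure chance. The Cluster randomization and intervention allocation section says that concealment was impractical, and women were enrolled individually within clusters, so recruitment could have differed by arm. That is fair, and the simulation, which assumes chance imbalance, does not cover it. But it argues for adjusting in every case, not for waiting to see a difference.

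Four stronger readings may tempt a reader, and the documents support none of them:

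- **The rule biases the result or inflates false positives.** For LAZ under randomisation it does neither.
- **Adjustment would be triggered by chance in nearly half of trials.** That needs a 5% test, a screen per contrast and independence. The first two are not in the text, and the shared comparison arm rules out the third.
- **Adjusting for height equals 4% to 19% more children** (1/(1 − r²) − 1). That holds only for more children in the same clusters. Between-cluster variance remains, so the standard error moves far less.
- **Leaving out height is an error.** The list is of possible confounders, and the article makes no statement about height that is wrong.

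**Conclusion.** The point holds as a matter of prespecification and modest precision. The document ties adjustment of its linear and logistic models, and possibly the Cox model, to an undefined judgement about baseline differences. The reported regression estimate therefore depends on how the baseline table happens to look and on who reads it.

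On the assumed R² values, always adjusting for the three named factors instead of following the rule raises power from 75% to 79% at a true effect of 0.3, and from 94.8% to 96.3% at 0.4. Height adds a 1% to 5% smaller standard error on the child-level assumption. The benefit is mainly narrower intervals and better power for effects below 0.4. These sizes rest on assumed correlations. That the rule has no criterion rests on the text alone. The change is worth making, but the trial's validity does not turn on it.

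**What to change.** Delete the condition. Before the 24-month data are analysed, state one covariate set for every arm comparison, whatever the baseline table shows: household food security, education, SES and randomisation block, plus maternal height as an already measured prognostic covariate. Define the form of each variable. Make the regression with a cluster random effect and this set the primary LAZ estimate, in place of the unadjusted t-test. Report the design-only model (arm, block and cluster) alongside. Say whether the Cox model uses the same set.

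No new data are needed, and follow-up was still under way at publication. The covariates cost a few degrees of freedom. Block costs more if entered as fixed terms: 24 for 25 blocks, taking the cluster-level total in one five-arm model from 125 − 5 = 120 to 96, which barely moves the critical value (1.980 to 1.985). In separate two-arm models it would go from 48 to 24, so a single joint model is preferable. A rule for missing covariate values is also needed.
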